### Blinding

Given the nature of the interventions, blinding operators and patients was unfeasible. However, the individuals responsible for data collection and analysis were blinded to the group information to guarantee objective and impartial results.

### Intervention Measures

#### Control Group

The patient received conventional hemodialysis treatment and care without any additional interventions.

Conventional hemodialysis treatment is the standard dialysis treatment regimen that includes general symptomatic support, including the selection of appropriate dialysis machines, fluids, and methods; blood pressure and blood sugar management; correction of anemia; and prevention of secondary hyperparathyroidism.

Conventional hemodialysis care consists of 3 distinct phases. First, predialysis care was administered, where patients were introduced to the dialysis room environment, and assistance was provided in assuming a comfortable position. Dialysis machines were checked for readiness, general condition was evaluated, and predialysis weight was measured. Second, during dialysis care, we closely monitored vital signs, observed the vascular access for swelling or bleeding, ensured tight connections of external blood circuits, and responded to dialysis machine alarms. Third, postdialysis care included managing the vascular access, assessing postdialysis conditions, providing health education on diet, re-examination, and daily protection of vascular access.

#### Acupoint Massage Group

##### Overview

In addition to conventional treatment and nursing, acupoint massage intervention was conducted 3 times a week, each lasting 15 minutes. Each acupoint was massaged for about 2‐3 minutes, focusing on specific acupoints, including Zusanli (ST36), Sanyin (SP 6), Taixi (KI3), and Yongquan (KI1).

Acupoints were selected based on an extensive literature review and expert consultation using the bone-degree measurement method in conjunction with finger-inch positioning. The location of the acupoints is based on the “National Standard of the People’s Republic of China GB/T 12346‐2021 Acupoint Names and Locations” [38]. Here are the locations of the following acupoints: (1) Zusanli (ST36) located on the lateral side of the lower leg, 3 cun below Dubi (ST35), on the line connecting Dubi (ST35) and Jiaxi (ST41), (2) Sanyinjiao (SP6) located on the medial aspect of the lower leg, 3 cun above the tip of the medial malleolus at the posterior border of the tibia, (3) Taixi (KI3) located in the depression between the tip of the medial malleolus and Achilles tendon on the inner side of the ankle, (4) Neiguan (PC6, nonfistula side) located on the anterior aspect of the forearm, 2 cun above the transverse crease of the wrist on the palmar side, between the tendons of the palmaris longus and the flexor carpi radialis, and (5) Hegu (LI4, nonfistula side) located on the dorsum of the hand between the first and second metacarpal bones, approximately at the midpoint of the radial side of the second metacarpal bone.

##### Intervention Time and Frequency

Acupoint massage was administered 15 minutes before the end of dialysis [39]. Each acupoint was pressed and rubbed with the fingers for approximately 2 minutes, with 100 compressions each. The intervention was performed 3 times per week. Patient-reported sensations, such as soreness, numbness, and distension, indicated that the acupoints were accurately located. The applied pressure was maintained within the limits of patient tolerance.

##### Intervention Method

Before enrollment, the research team provided patients with a comprehensive introduction to the acupoints for pressing, including their functions and associated precautions. This ensured patient acceptance and cooperation. The acupoint pressing procedure was performed by trained members of the research team. Patients were reminded of the specific locations and functions of the acupoints during the procedure. The applied pressure was carefully adjusted to remain within the tolerance levels of the patients.

The force was applied uniformly and gently to prevent skin damage. The patient’s subjective sensations were closely monitored throughout the procedure, and the patients were observed for any signs of injury, erythema, or edema on the skin. To avoid discomfort, massage should be avoided when the patient experiences anxiety, hunger, or over-satiation.

### Sitting Baduanjin Combined With Acupoint Massage Group

In addition to conventional treatment and care, the patients received combined sitting Baduanjin exercise and acupoint massage thrice weekly. Each session comprised 30 minutes of Baduanjin exercise and 15 minutes of acupoint massage. The steps of Baduanjin are detailed in Table 1.

**Table 1. T1:** The steps of Baduanjin.

Steps	Exercise name	Key movements and steps	Duration and frequency	Body posture tips
First step	Sit with eyes closed to calm the mind	Sit with eyes closed and back straight; fists on knees and tongue touching upper palate. Abdominal breathing and gather qi at Dantian (3‐5 min). Tap teeth 36 times and swallow saliva in 3 mouthfuls. Interlace hands to hold neck and breathe 9 times. Flick back of head 24 times (such as drumming).	3‐5 minutes (sitting quietly), 36 times (tooth tapping), 9 times (breathing), and 24 times (head flicking)	Cross-legged or legs hanging, back straight, and tongue against upper palate
Second step	Slightly swing and shake the “Tianzhu”	Interlace hands (palms up) at thigh roots. Lower head and twist neck to look left and right backward; swing shoulders with neck movement.	24 times per side	Keep upper body relaxed, coordinate neck, and shoulder movements
Third step	The “Red Dragon” stirring to produce saliva	Stir tongue in mouth (up, down, left, and right) to make saliva. Swirl saliva 36 times and swallow in 3 mouthfuls (with gurgling sound).	36 times (swirling) and 3 mouthfuls (swallowing)	Mouth closed, tongue movement gentle, and full
Fourth step	Hold breath, rub hands to warm them, and massage the back	Inhale and hold breath; rub hands until warm and massage lower back sides while exhaling. Repeat 24 times and then clench fists. Inhale and hold breath; imagine fire burning Dantian and exhale.	24 times (massage cycle) and 1 round (breath-holding and imagination)	Keep waist straight during massage and focus on dantian when imagining fire
Fifth step	Single-side “Pulley” rotation	Place 1 hand on corresponding waist (left hand on left waist and right hand on right waist). Lower head and move arm in a circle (back to front) such as a pulley.	36 times per side (left arm first and then right arm)	Arm movement smooth and keep body stable without leaning
Sixth step	Double-side “Pulley” rotation	Place both hands on waist. Lower head and move shoulders and arms in a circle simultaneously, such as a pulley. Straighten legs and rest 1 minute after movement.	36 times (circular movement) and 1 minute (rest)	Shoulders and arms move in sync and relax fully during rest
Seventh step	Cross-legged sitting with hands lifted above the head	Rub hands and exhale on palms 5 times. Interlace fingers, turn palms up, and lift hands over head; stretch waist upward. Slowly lower arms.	9 times (lifting and lowering cycle)	Sit cross-legged and stretch body fully when lifting hands and lower arms slowly
Eighth step	Lower the head and reach for the feet frequently	Palms facing each other and stretch hands forward. Bend upper body forward, grasp foot soles, and lean forward and lower head. Slowly sit up straight. After 12 repetitions: cross-legged sit, clench fists, and calm mind; swirl saliva 36 times and swallow in 6 mouthfuls.	12 times (bending and sitting up), 36 times (saliva swirling), and 6 mouthfuls (swallowing)	Bend body slowly to avoid sudden force and keep breath natural during movement

#### Intervention Schedule and Frequency

The integrated intervention protocol involved conducting sessions 3 times per week, with each session lasting 45 minutes. The duration was allocated as follows: 30 minutes for sitting Baduanjin exercises and 15 minutes for acupoint massage.

#### Intervention Methods and Preparation

A comprehensive health promotion manual focusing on sitting Baduanjin exercises and acupoint massage was developed. The manual primarily included the benefits of this integrated therapy for patients undergoing dialysis, as well as detailed implementation plans and specific techniques, exercise principles, and protocols for managing any physical discomfort that may arise.

On the day of enrollment, the sitting Baduanjin technique and associated acupoints were explained to the patients. The purpose, methodology, expected outcomes, and precautions of this integrated therapy were elaborated to ensure their understanding and cooperation. After confirming through questioning that the patients had comprehended the relevant information, the necessary materials, including forms, brochures, and a recorded video demonstrating the sitting Baduanjin practice, were distributed.

### Stage of Clinical Implementation

First, for the intervention content, a centralized intervention approach was implemented. The intervention sessions were conducted on dialysis days, 45 minutes before the start of dialysis, in the department’s health education room. Participants engaged in group practice of sitting Baduanjin exercises. Each session was supervised by 2 research team members: one demonstrated and explained the movements and breathing techniques, while the other provided real-time corrections to ensure proper form. Efforts were made to standardize movements within the participants’ physical capabilities to maximize exercise efficacy. The intervention was administered 3 times per week, with each session lasting 30 minutes and divided into 3 segments: a 3-minute warm-up focusing on joint mobility, a 25-minute main segment where sitting Baduanjin was practiced following standardized fitness qigong music instructions under the guidance of research team members, and a 2-minute cool-down period dedicated to relaxation and stretching exercises. In addition, 15 minutes before the end of dialysis, acupressure was applied to bilateral Zusanli (ST 36), Sanyinjiao (SP 6), Taixi (KI 3), and Neiguan (PC 6) on the nonfistula side, and Hegu (LI 4) on the nonfistula side. Following treatment, the participants rested for 15 minutes before leaving the dialysis room.

Second, the following precautions were taken: during the exercise regimen, if the patient experiences any of the following symptoms, which are severe fatigue, chest pain, hypoglycemic episodes, arrhythmia, shortness of breath, hypotension, or other abnormal conditions, the activity must be stopped immediately, and appropriate emergency protocols must be initiated.

As the closing form, the practitioner assumes a seated posture with their hands naturally hanging down and then adjusts their breathing.

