### Statistical Methods

#### Statistical Analysis

The database was established using Microsoft Excel software, and SPSS (version 25.0; IBM Corp) was used for statistical analysis and processing of all data. A bilateral test was used for statistical analysis; *α*=.05 was used as the test level, and *P*<.05 was considered statistically significant.

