#### Statistical Inference

Baseline characteristics were comparable across groups. Continuous variables were analyzed using one-way ANOVA (normally distributed data) or rank-sum test; categorical data were assessed with chi-square tests. Within-group pre-post comparisons used paired 2-tailed *t* tests (normal data) or rank-sum tests. Between-group differences postintervention were evaluated using one-way ANOVA (with least significant difference post hoc testing if significant) or rank-sum tests, as appropriate. Categorical outcomes were compared using chi-square tests.

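### Group-taught exercise in the combined arm only is analysed as if all patients were independent; the overall F test, and combined versus massage if massage works, can exceed 5%

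*Protocol article*

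**What the plan says.** Only one arm receives the exercise. Under Sitting Baduanjin Combined With Acupoint Massage Group, "the patients received combined sitting Baduanjin exercise and acupoint massage thrice weekly". Stage of Clinical Implementation describes delivery before dialysis in the department's health education room: "Participants engaged in group practice of sitting Baduanjin exercises", and "Each session was supervised by 2 research team members". At 3 sessions a week for 8 weeks, a patient can attend up to 3 × 8 = 24 group sessions.

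The other arms have no described group element. For controls, "The patient received conventional hemodialysis treatment and care without any additional interventions". For massage, "The acupoint pressing procedure was performed by trained members of the research team", near the end of dialysis.

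Statistical Inference fixes the comparison: "Between-group differences postintervention were evaluated using one-way ANOVA (with least significant difference post hoc testing if significant) or rank-sum tests". Statistical Analysis sets a two-sided 0.05 level. Neither section has a term for exercise group, and Sample Size Calculation contains no design effect.

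**The concern.** This is an individually randomised trial with group delivery in one arm. Patients who practise together may come to share influences, such as group atmosphere, mutual encouragement or attendance habits, that make their outcomes more alike. The variance of the combined-arm mean then contains a between-group part that ANOVA, LSD and rank-sum tests leave out.

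The Conclusions set the combined treatment against routine care and against massage alone. Both contrasts use the arm with group delivery. At stake is whether a difference arising from a few exercise groups could be reported as benefit of the exercise at P<.05.

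**Working it through.** **Inputs from the article.** Two-sided α = 0.05; power 0.90; n = 34 per arm, 38 after 10% dropout; FRAIL means 3.29, 2.67, 2.58 and SDs 0.96, 0.87, 1.02 (Sample Size Calculation, arms not labelled); LSD only after a significant F (Statistical Inference).

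**Assumptions.** 36 analysed per arm, lying between 34 and 38; ICC 0.05 to 0.10; 4 to 18 equal groups in the combined arm.

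**1. The plan's own figures.** With ICC 0, the simulated F test rejects in about 5% of null trials, as stated. The printed n does not reproduce. Mean variance = (0.9216 + 0.7569 + 1.0404)/3 = 0.9063; between-mean term = 0.2989/2 = 0.1494; n = 2.52² × 0.9063/0.1494 = 38.5, so 39 rather than 34. That is a separate matter on which this point does not depend.

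**2. Comparison with the combined arm, without the F condition.** Design effect in the combined arm: DE = 1 + (m − 1) × ICC, for groups of size m. True two-sided error of a nominal 5% comparison with another arm: 2 × [1 − Φ(1.96/√((1 + DE)/2))].

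Example: 6 groups of 6, ICC 0.10. DE = 1 + 5 × 0.10 = 1.50; √1.25 = 1.118; 1.96/1.118 = 1.753; error = 8.0%.

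| Groups × size | ICC 0.05: DE, error | ICC 0.10: DE, error |
|---|---|---|
| 4 × 9 | 1.40, 7.4% | 1.80, 9.8% |
| 6 × 6 | 1.25, 6.5% | 1.50, 8.0% |
| 9 × 4 | 1.15, 5.9% | 1.30, 6.8% |
| 12 × 3 | 1.10, 5.6% | 1.20, 6.2% |
| 18 × 2 | 1.05, 5.3% | 1.10, 5.6% |

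For groups of 2 or 3, simulation gives about 5.3 to 6.4%. With 20,000 runs the simulation error near 6% is √(0.06 × 0.94/20,000) = 0.17 points, so this agrees with the formula.

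**3. The planned procedure, all arms equal.** The simulated F test rejects in 5.9 to 9.4% of trials at 4 to 9 groups. Combined versus control, tested only after a significant F, starts near 2.5% at ICC 0 and rises as follows:

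| Groups | ICC 0.05 | ICC 0.10 |
|---|---|---|
| 9 | 3.2% | 3.9% |
| 6 | 3.5% | 4.6% |
| 4 | 4.2% | 5.9% |

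**4. The planned procedure when massage works and exercise adds nothing.** Take 3.29 as control and 2.67 as massage (an assumed labelling), with the combined arm equal to massage. The F test is significant in about 81% of trials, so the condition gives little protection. Combined versus massage then rejects falsely in about 5.9 to 9.3% at 4 to 9 groups.

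**5. How large could groups be?** Combined-arm patients in treatment at once ≈ arm enrolment × 8 weeks ÷ accrual weeks, assuming even allocation:
- Abstract: 52 enrolled, August 2024 to August 2025. 17.3 × 8/52 = 2.7.
- The same 52 counted from the December 2024 start in Results, about 8 months or 34.7 weeks. 17.3 × 8/34.7 = 4.0.
- All 38 over about 11.5 months, or 49.8 weeks. 38 × 8/49.8 = 6.1.
- The remaining 62 in about 15 weeks to the end of November 2025. 20.7 × 8/15 = 11.0.

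So about 3 to 11 patients at once, before any division by dialysis day and slot, and with rolling entry.

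**6. Power.** With 34 per arm, SD √0.9063 = 0.952 and a difference of 3.29 − 2.58 = 0.71 (same assumed labelling), z = (0.71/0.952)/√(2/34) = 3.075, and power is Φ(3.075 − 1.96) = 0.87. At ICC 0.05 with 4 groups, DE = 1 + 7.5 × 0.05 = 1.375, so Φ(3.075/√1.1875 − 1.96) = 0.81.

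**The case against.** A reader might infer that every comparison involving the combined arm exceeds 5%. The plan does not support that: LSD follows only a significant F, and with all arms equal the pairwise error stays below 5% over most of the assumed range. The condition does not protect the F test itself, or combined versus massage once massage works.

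A reader might also take it as established that the standard errors are too small. That needs a positive ICC, and none is given. Nor do shared instructors prove it. The article does not say that different pairs taught different groups; if one pair taught everyone, their effect is common to the whole arm and no group term would capture it.

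Fixed groups of 4 to 9 patients sit poorly with the accrual, which points to small groups with rolling entry. That stands, and it moves the likely excess to the lower range. At ICC 0.01 to 0.02 with 8 groups the error is only 5.2 to 5.4%.

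Finally, an analysis plan that is not shown may add a group term. But the article does more than leave the model open: it names tests that do not match the delivery it describes.

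**Conclusion.** The mismatch between delivery and analysis is in the text; its size is not. At ICC 0.05 to 0.10 with 36 per arm, expect a true error of about 5.3 to 6.4% for groups of 2 or 3, and about 6 to 9% for 4 to 9 fixed groups. This applies to the F test and, when massage truly differs from control, to combined versus massage. With all arms equal, pairwise error passes 5% only at about ICC 0.10 with 4 groups. Control versus massage stays at about 5%. If the ICC is near zero, nothing material changes. The point merits a cheap safeguard and does not invalidate the design.

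**What to change.** - From the dialysis roster, record each combined-arm patient's exercise slot and calendar period.
- In Statistical Inference, adjust the between-arm comparison for the baseline score already collected. This does not remove clustering.
- Add a partially nested mixed model, at least as a prespecified sensitivity analysis: fixed effects for arm and baseline score, a random exercise-group intercept in the combined arm only, and Satterthwaite degrees of freedom. Report the ICC. If the group variance is estimated as zero, it reduces to the ordinary model.
- State in Sample Size Calculation that the power assumes no group effect.

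The Results section places the effect analysis after data collection, so this can be fixed beforehand. The cost is a roster field, one model, and slightly wider intervals for combined-arm comparisons: about 2 to 7 points of power at 4 to 9 groups if there is no group effect. Under rolling entry, slot and period only approximate the true exercise group, and the report should say so.

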### Adverse Event Monitoring Plan

Trained nurses recorded adverse events (AEs; hypotension, arrhythmia, etc) via real-time vital sign monitoring (every 30 minutes during dialysis) and patient-reported symptoms. AEs were graded using Common Terminology Criteria for Adverse Events (version 5.0) and reported to the principal investigator within 2 hours; severe AEs were reported to the ethics committee within 24 hours.

### Intervention Pause Criteria

Interventions were paused immediately if (1) systolic blood pressure was <90 mmHg (persistent after fluid resuscitation), (2) new-onset ventricular arrhythmia, and (3) patient-reported severe discomfort (eg, chest pain). The principal investigator would reassess within 1 hour to decide resumption or termination.

### Evaluation Indicators

#### Overview

Data collection will be conducted in strict accordance with the established schedule to ensure the integrity and timeliness of information. Research team members must be trained in standardized measurement methods to minimize measurement bias. Furthermore, baseline data (including demographic characteristics, FRAIL scale scores, grip strength, 10 times sit-to-stand (STS-10) results, Self-Rating Depression Scale (SDS) scores, and QoL (Short Form Health Survey Questionnaire [SF-36]) scores must be collected before the intervention, and follow-up data for the same indicators must be collected after 8 weeks of treatment. The specific research program, including the timing of enrollment, intervention implementation, and indicator assessment, is detailed in Table 2.

**Table 2. T2:** Enrollment schedule, interventions, and evaluation.

Research period	Registration phase (1 week)	Divide into groups (>1 week)	Intervene (8 weeks)
Point in time			
Join a group	✓		
Eligibility screening	**✓**		
Informed consent	**✓**		
Divide into groups		**✓**	
Intervene			
Control group			✓
Routine treatment and nursing			**✓**
Routine treatment and nursing+acupressure group			**✓**
Conventional treatment and nursing+sitting Baduanjin combined acupressure			**✓**
Assessment			
FRAIL^a^ Scale score			**✓**
Grip strength			**✓**
STS-10^b^			**✓**
SDS^c^			**✓**
SF-36^d^			**✓**

a FRAIL: Fatigue, Resistance, Ambulation, Illness, and Weight Loss.

b STS-10: 10 times sit-to-stand.

c SDS: Self-Rating Depression Scale.

d SF-36: Short Form Health Survey Questionnaire.

#### Primary Evaluation Indicator (FRAIL Scale Score)

To assess the severity of frailty in patients, the scores before and after the intervention were compared as follows.

Decline: the FRAIL scale, a simple frailty measurement tool developed by the International Society for Nutrition and Aging in 2008 and derived from the Fried Frailty Scale, which has been widely used in different populations, is quick and easy to use and predicts the occurrence of adverse outcomes. The scale consists of 5 entries: fatigue, increased resistance or decreased endurance, decreased free mobility, disease conditions, and decreased body mass. Each entry was assigned 1 point, and the total score ranged from 0 to 5, with 0 indicating no debility, 1‐2 indicating debilitating, and ≥3 indicating debilitating. A large foreign cohort study confirmed the good predictive validity of the FRAIL scale for impairment of daily activities and the occurrence of death [40]. Compared with other debilitation measurement tools, the FRAIL scale is most closely associated with dialysis-related complications and is useful for screening for debilitation in patients undergoing MHD [41]. It was standardized by Wei et al [42], and its reliability and validity were good, with a Cronbach coefficient of 0.826 and content validity of 0.98.Indicators of somatic function: due to the lack of objective indicators on the FRAIL scale, secondary evaluation indicators related to physical function were selected for measurement based on the literature review.

#### Secondary Evaluation Indicators

##### Grip Strength

Hand grip strength testing is the simplest and most widely used method for upper limb muscle strength testing. In this study, the EH101 electronic grip strength meter (Guangdong Xiangshan Company) was used to measure the grip strength. The patients were asked to hold the grip strength meter with maximum force using the noninternal fistula side of the limb in a standing position during measurement. Overall, 2 measurements were taken, with a 15-second interval between each measurement. The average value of the 2 measurements was taken.

